# Study Summary

| **Study Title** | The NICU Antibiotics and Outcomes Trial (NANO) |
| --- | --- |
| **Study Design** | Randomized, placebo controlled, double blinded multicenter trial |
| **Primary Objective** | To compare the incidence of late onset sepsis (LOS), necrotizing enterocolitis (NEC), and death in premature infants ≤28 weeks gestation randomized to receive empiric antibiotics (EA) or placebo at birth. |
| **Secondary Objective(s)** | To compare early patterns of gut microbial colonization in premature infants ≤28 weeks gestation randomized to receive empiric antibiotics (EA) or placebo at birth. |
| **Research Intervention(s)/ Investigational Agent(s)** | The intervention consists of administering ampicillin and gentamicin at site approved dosing guidelines OR a volume matched equivalent of normal saline. |
| **IND/IDE #** | IND Exempt (PIND 143353) |
| **Study Population** | Newborn infants born at participating study sites with gestational age of 23-28 weeks |
| **Sample Size** | 802 |
| **Study Duration for individual participants** | Duration of index hospitalization |
| **Study Specific Abbreviations/ Definitions** | **ELBW-** Extremely Low Birth Weight Infants  **LOS**- Late Onset Sepsis  **NEC**- Necrotizing Enterocolitis: A disease that affects mostly the intestine of premature infants. The wall of the intestine is invaded by bacteria, which can cause local infection and inflammation that can destroy the intestinal wall.  **EA**- Empiric Antibiotics  **EOS-** Early Onset Sepsis  **NICU-** Neonatal Intensive Care Unit  **NIH-** National Institutes of Health  **AE-** Adverse Event  **SAE-** Serious Adverse Event  **IND**- Investigational New drug  **IDS**- Investigational Drug service  **IRB-** Institutional Review Board  **HHS-** Health and Human Services  **DSMB-** Data and Safety Monitoring Board  **MOP-** Manual of Procedures  **DCC-** Data Coordinating Center |

# Objectives and Aims

# The goal of the NANO Trial is to test the hypothesis that the rate of adverse outcomes is higher in ELBW infants receiving EA compared to infants receiving placebo. We have three aims:

# Aim 1. To test the hypothesis that the composite incidence of LOS, NEC, and/or death is significantly different in infants that receive EA and infants that receive placebo.

Aim 2. To test the hypothesis that fecal samples in the first month of life from infants receiving EA will contain lower diversity, higher abundance of pathogens, and lower abundance of commensal anaerobes than fecal samples from infants receiving placebo.

Aim 3**.** (Exploratory) To identify microbial taxa associated with delayed or accelerated somatic growth (weekly weight and length z-scores) during the first month of life in infants receiving placebo or EA.

# Background

# Early onset sepsis (EOS) is a rare but morbid bloodstream infection that can occur in newborn infants during the first 3 days of life. Timely diagnosis of EOS is challenging in extremely low birthweight infants since there are no accepted biomarkers for the disease and because the clinical signs of EOS (e.g. respiratory failure) can overlap with common non-infectious physiologic derangements in preterm infants. As a result, the standard of care in many NICUs is to administer empiric antibiotics (EA) to preterm infants during the first 2-7 days of life or until a workup for EOS is complete^9–11^. Population-based studies have consistently shown that 80-90% of extremely low birthweight (ELBW) infants receive EA despite an EOS incidence of 2% or less^12–14^.

# It is increasingly recognized that adverse effects of antibiotics extend beyond the well-recognized problem of antibiotic resistance to include unintended clinical consequences related to eradication of the human microbiota. Several recent studies in preterm infants have identified associations between early antibiotic exposure and adverse events including necrotizing enterocolitis (NEC) and late onset sepsis (LOS)^15–24^. For these reasons, antibiotic stewardship initiatives have been widely adopted in NICUs and indeed they have successfully reduced the length of EA therapy – however nearly all ELBW infants continue to receive at least a short course of EA at birth. It is generally accepted that published guidelines on the subject are outdated^25^, and therefore it is not surprising that EA practice patterns (e.g. length of therapy) vary wildly among providers and across centers^12,26–28^.

Our multidisciplinary team has more than 10 years of experience monitoring temporal changes in the gut microbiota of preterm infants^32–44^. In previous studies, we have documented that EA exposure is associated with unambiguous changes in the microbiota favoring growth of pathogens^10–23^. Our preliminary data supports published studies demonstrating a dose-dependent relationship between EA and a composite outcome of LOS, NEC, or mortality^45^. We and others have also described associations between antibiotics, gut bacterial colonization patterns, and infant growth^46,47^.

Completion of this trial may position us to conclude that EA therapy **worsens** outcomes or that EA **improves** outcomes in premature infants. If the former is true, results could rapidly be translated into a decrease in antibiotic usage in NICUs. Should we find *improved* outcomes with antibiotic administration, this trial would provide physicians with confidence to continue administering EA – a common practice at present despite a lack of high quality data. It is also possible that significant differences will **not** be observed between study arms and, depending upon the details, this result may itself be useful to care providers.

# Study Endpoints

# Primary Outcome: Composite incidence of adverse outcomes (NEC, LOS, or death during the index hospitalization).

# NEC will be defined strictly by Bell’s stage II or III criteria for moderate or advanced NEC^50^. To reduce overlap between NEC and diagnosis of spontaneous intestinal perforation, the diagnosis of NEC will only be considered in infants > 7 days of age. LOS is defined as a positive blood culture obtained after 72 hours of life and intent to treat with antibiotics for 5 days or more^195^. Death is defined as death during the index hospitalization.

Secondary Outcomes: NEC during the index hospitalization, LOS during the index hospitalization, or death during the index hospitalization.

# Study Intervention/Investigational Agent

Once maternal and infant eligibility are established, infants will be randomized into one of two different study groups: receiving conventional empiric antibiotics (ampicillin and gentamicin) or placebo while completing an evaluation for early onset sepsis. It is essential that randomization occurs within the first 4 hours of life.

All key resources for this proposal will be authenticated to enhance the reproducibility of our data, as appropriate and according to NIH policy (Notice Number: NOT-OD-17-068). Antibiotics used in this clinical trial will be commercially available pharmaceuticals sourced individually at each study site and administered to investigative pharmacy SOPs specific to each site. Lot numbers will be tracked to aid in identifying reagents that may be performing outside acceptable limits.

# Procedures Involved

# The NANO trial has been designed to study the longstanding clinical practice of empirically administering intravenous antibiotics to extremely low birthweight (ELBW) infants in the first days of life. It is an 802-subject multicenter placebo-controlled double-blinded randomized clinical trial to test the hypothesis that the incidence of adverse outcomes is higher in babies receiving EA in the first week of life compared to babies receiving placebo. We target a population of ELBW infants in whom the clinical decision to use or not use EA is currently most challenging -- infants that are clinically stable that did not have a known exposure to intraamniotic infection and were not born preterm for maternal indications.

# 6.1 Randomization and Blinding*.* For each infant born to a mother that has provided consent, eligibility will be assessed. One consent document is sufficient for both the mother and her baby. Thus, there will be a two-part screening to first determine maternal eligibility, and then to determine infant eligibility. IRB approved staff will screen infants based on inclusion/exclusion criteria. The site coordinator, or research staff, will discuss eligibility with approved staff and if the patient is eligible, input patient data into the web based system. Once data is inputted, research staff will randomize eligible families 1:1 using web-based block randomization stratified by study site to receive EA or placebo. Multiples (i.e. siblings) will be randomized to the same treatment arm. Staff will not see the treatment arm that patients are assigned to. Rather, treatment arm and patient information will be sent to each site’s investigational pharmacy, where study drug will be drawn and sent to the patient’s room. The staff member who performed randomization will see a confirmation message that randomization was successfully sent to the pharmacy. The investigational pharmacy is unblind to patient’s allocation. Participants, treating clinicians, and study staff will all be blinded to allocation. Randomization must occur within the first 4 hours of life. Outcome assessors and statistical summaries for trial monitoring will be unaware of group allocation. Unblinded data evaluation during the trial will be restricted to a designated study statistician and the DSMB. We will unblind investigators and begin analyses only after all data collection forms are completed, data queries resolved, and data are locked for analysis.

# 6.2 Study Procedure*.* The intervention consists of administering either conventional EA or placebo while completing an evaluation for early onset sepsis. Each site will source antibiotics individually. Either conventional EA or placebo must be given intravenously within 120 minutes following randomization. If EA is given, it will consist of ampicillin and gentamicin administered according to local, site-approved dosing guidelines clearly reflected in each site’s SOP. Infants randomized to receive placebo will receive volume-matched equivalents of normal saline matching the analogous schedule of ampicillin and gentamicin administration.

6.3 Rescue antibiotics. We anticipate that <<5% of study subjects will experience worsening of conditions prompting clinicians to order additional antibiotics that will be termed "rescue antibiotics." Clinicians will have complete freedom to repeat blood cultures and to order the antibiotics that they feel are most appropriate to treat the infant, with no restrictions imposed by the study protocol. This is a specific safety measure for NANO but is fully consistent with the standard of care for infants experiencing clinical deterioration. Should this occur, the treating physicians will remain blinded to the initial study drug assignment. The study pharmacist will be unblinded. Patients who have received a rescue option will continue to be followed until discharge from the NICU.

# Rescue antibiotic therapy. There are two primary scenarios -- both rare -- that may be encountered requiring rescue antibiotic therapy.

# The first scenario may occur if an Attending Neonatologist wishes to guarantee the infant actually receives ampicillin and gentamicin and not only placebo. To accomplish this, a second set of study drug orders will be placed while the original study drug orders are continued. For the second set, if the original assignment was placebo, pharmacy will prepare ampicillin and gentamicin. If the original assignment was ampicillin and gentamicin, pharmacy will prepare placebo and placebo. Sites that give ampicillin every 8 hours according to their local standard of care can elect to provide blinded active ampicillin as rescue antibiotic instead of both placebo and ampicillin in order to reduce daily drug administration burden. This would not affect the gentamicin rescue, which is only a single dose.

# The order and label for rescue antibiotics should include some rescue status indicator to avoid preparation/dispensing/administration errors. If this rescue antibiotic scenario occurs, providers will have a guarantee that the infant is receiving ampicillin and gentamicin. Providers will not know what the initial order set consisted of, in order to maintain blinding. The second set of orders should discontinue at the same time as the first round of orders. The schedule for subsequent ampicillin doses after the study period has ended (if desired) would be based on the timing of the split difference between the last study placebo and active ampicillin administrations. The schedule for subsequent gentamicin doses will be based on local standard therapeutic drug monitoring.

# The second rescue scenario will involve a decision by an Attending Neonatologist to empirically treat suspected/confirmed bacterial threats not optimally covered by ampicillin and gentamicin (e.g. penicillin for syphilis, ceftriaxone for gonorrhea, azithromycin for chlamydia, vancomycin or nafcillin for Staph, meropenem or cefepime for MDR GNR) with open label non EA antibacterials. These are ordered outside of the study and are not the responsibility of the IDS. Routine Candida prophylaxis (e.g. fluconazole) is not considered an open-label antibacterial for the purposes of this study and its use is not viewed as rescue therapy.

#

# 6.4 Early Discontinuation of EA. Study drugs can be discontinued at the discretion of the Attending Neonatologist prior to the completion of the study period, just as EA therapy might normally be discontinued outside the context of the trial. The Attending Neonatologist should ideally discuss their desire to discontinue study drugs early with the PI and research team before doing so. Potential reasons for discontinuing study drugs include:

# •The Attending wants the participant to receive rescue antibiotic therapy (see above).

# •They have decided that EA treatment is no longer necessary for clinical care (e.g. blood culture negative and no clinical concern for infection).

# Ordering and administering antibiotics after the study period is at the discretion of the Attending Neonatologist. In such cases, NICU prescribers will place new orders for these antibiotics per routine care. IDS is not responsible for these antibiotics since they are beyond the study period and the participant has completed the study drug therapy. The NICU treatment team will decide their dosing and start times. A sensible approach would be to stay on the same schedule as the study drugs. If the participant was previously converted to blinded EA, the start time can be the split difference between the two sets’ schedules. Gentamicin plasma concentration monitoring may be used to help with determining start times (see next section). Prescribers will not be unblinded to determine these start times. They should remain blinded and should not count study doses towards the total days of therapy that the baby ultimately receives.

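### Sections 6.3 and 6.4 of the protocol contradict each other on whether the original study drug continues when rescue is wanted, and the promised rescue guarantee depends on the answer

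*Protocol*

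**What the plan says.** Protocol Section 6.3 describes two rescue scenarios under the common name of rescue antibiotic therapy.

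- Scenario 1 applies "if an Attending Neonatologist wishes to guarantee the infant actually receives ampicillin and gentamicin and not only placebo". In that case "a second set of study drug orders will be placed while the original study drug orders are continued". The content of the second set depends on the original assignment. A placebo-arm infant gets the active drugs. For the other arm, "If the original assignment was ampicillin and gentamicin, pharmacy will prepare placebo and placebo". Section 6.3 then states that "providers will have a guarantee that the infant is receiving ampicillin and gentamicin", and adds: "The second set of orders should discontinue at the same time as the first round of orders".
- Within scenario 1, sites that dose ampicillin every 8 hours may instead give blinded active ampicillin as the rescue. The gentamicin rescue, described as a single dose, is unaffected by this option.
- Scenario 2 treats threats that ampicillin and gentamicin do not cover well, "with open label non EA antibacterials", ordered outside the study. The text does not say whether study drug continues.

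Section 6.4 (Early Discontinuation of EA) introduces its list with "Potential reasons for discontinuing study drugs include". The first entry is "The Attending wants the participant to receive rescue antibiotic therapy (see above". It does not say which scenario is meant.

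**The concern.** Scenario 1 exists to give a worried attending certainty that the infant is on active drug without breaking the blind. In the EA arm the second set contains no active drug, so the certainty comes entirely from the first set. A rule that treats the wish for rescue as grounds for stopping the first set removes what the guarantee depends on.

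The prescriber cannot detect this, because treating physicians stay blinded to the assignment and are told that the guarantee holds. Section 6.3 presents rescue as a specific safety measure of the trial. Section 14.1 rests the acceptability of placebo partly on the trial not obstructing any care an infant needs. An instruction that can be read in a way that defeats that measure is therefore a safety matter, even if the situation is rare.

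**Working it through.** No sample-size, power or alpha figure bears on this point. The check is to cross the two arms with the two instructions about the original orders and, where those orders are stopped, with the two possible fates of the second set.

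Inputs, all from the protocol:
- content of the second set by arm, and continuation of the original orders: Section 6.3, scenario 1;
- second set stops when the first stops: Section 6.3, the paragraph on rescue orders and labels;
- wish for rescue as a reason to stop study drug: Section 6.4, first bullet.

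| Arm | Original orders | Second set | What the infant receives from then on | Guarantee |
|---|---|---|---|---|
| EA | continue (6.3) | placebo | active + placebo | met |
| Placebo | continue (6.3) | active | placebo + active | met |
| EA | stopped (6.4) | runs on, placebo | placebo only | broken |
| Placebo | stopped (6.4) | runs on, active | active | met |
| EA | stopped (6.4) | stops with the first (6.3) | no study drug | broken |
| Placebo | stopped (6.4) | stops with the first (6.3) | no study drug | broken |

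The guarantee holds in both arms only when the original orders continue. Once 6.4 is applied to a scenario-1 rescue, it fails in the EA arm if the second set runs on, and in both arms if the stop-time sentence is followed.

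Two features of Section 6.3 narrow the third row:
- Under the 8-hourly option the rescue ampicillin is itself active, so an EA-arm infant at such a site would still receive active ampicillin. The gentamicin part is not changed by the option.
- The gentamicin rescue is a single dose, and doses given before the stop are not undone. What is at risk is mainly the remaining ampicillin doses.

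Does 6.4 have scenario 1 in view? Its bullet uses the term that 6.3 applies to both scenarios. Later in 6.4, the text on antibiotics after the study period refers to infants already converted to blinded EA and to the schedules of two sets, which describes scenario 1. The bullet therefore cannot be confined to scenario 2 on the wording alone.

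**The case against.** The strongest reply is that the harmful path requires a specific rule to be set aside in favour of a permissive one. Scenario 1 says plainly that the original orders go on; 6.4 only lists possible reasons for stopping and does not tell anyone to stop the first set when ordering the second. The bullet also has sensible referents. In scenario 2, stopping study drug defeats no guarantee. Under the 8-hourly option, one active ampicillin order replaces two parallel ones. This is a reasonable guess at what was intended, but the document does not say it.

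There are also safeguards. The pharmacist is unblinded, rescue orders and labels should carry an indicator, the attending should ideally speak to the research team before stopping, and clinicians may order any antibiotic they wish. These make the outcome less likely. None is a required check for this error, however. The dispensing rule depends only on the original assignment, so a pharmacist who follows it prepares placebo for an EA-arm infant. A clinician who believes the guarantee holds has little reason to order more.

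Three stronger readings are tempting, and the documents do not support them:
- **That every such infant in the EA arm would be left on saline.** This also requires departing from the stop-time sentence. If that sentence is followed, both sets end, in either arm. The problem is therefore not strictly one-directional.
- **That about 20 EA-arm infants are at risk.** That figure is 0.05 × 401 = 20.05. It takes as the rate a bound that the protocol says is far above what it expects (<<5%). It also counts both scenarios and assumes that 6.4 is applied in every case.
- **That the primary composite is biased against EA.** The components (Section 4) are late-onset sepsis on cultures after 72 hours, necrotizing enterocolitis after 7 days, and death during the index hospitalization. Nothing in the protocol links a few missed doses in a very small subset to a material shift in the risk ratio.

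**Conclusion.** The contradiction is in the current text and the concern stands as a safety point. Sections 6.3 and 6.4 give opposite instructions on the original study drug when rescue is wanted, and applying 6.4 to a scenario-1 rescue breaks the guarantee on either reading of what happens to the second set.

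The conclusion is conditional: it describes what could happen where 6.4 is applied to scenario 1, not what will happen. It assumes that the bullet is read as written, without restriction to scenario 2, and that no undocumented pharmacy check intervenes. The number of infants affected cannot be derived from the protocol and is likely small. No effect on the primary analysis is claimed.

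**What to change.** The sponsor must reconcile Sections 6.3 and 6.4. For each case (scenario 1 with a blinded second set, scenario 1 under the 8-hourly ampicillin option, and scenario 2 with open-label antibacterials), state whether the original study-drug orders continue or stop. Then make three pieces of text agree with that statement: the pharmacy dispensing rule for the second set, the rescue bullet in 6.4, and the sentence tying the second set's end to the first's. Which clinical rule is right is for the clinical team; the request is only that the protocol state one rule per case.

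The cost is a protocol clarification, a letter to sites and an update of the pharmacy instructions. Sample size and analysis are unaffected.

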# 6.5 Gentamicin plasma concentration monitoring. It is expected that a small percentage of participants will receive gentamicin after the study period. This will trigger site-specific procedures for routine care gentamicin therapeutic drug monitoring, the results of which will may make it possible for blinded providers and staff to discern group allocation. This is expected and unavoidable. Pharmacists who routinely perform clinical pharmacokinetics in the NICU should therefore be part of the unblinded study pharmacist team. If allowed by site practice standards, clinical PK assessments that include dosing histories may be kept with the participant’s Dispensing Log rather than in their medical chart, in order to minimize the risk of unblinding.

